## Abstract

**Background:**

Curcumin, a derivative of the spice turmeric, has been adopted by Eastern medicine for centuries as an adjunct to treat several medical conditions (e.g., anorexia and arthritis) because of its well-established anti-inflammatory properties. Studies have shown that the use of curcumin in mice models has led to reduction in several inflammatory markers as well as key inflammatory pathway enzymes. As a result, studies in Western medicine have developed to determine if this recognized benefit can be utilized for patients with inflammatory lung diseases, such as asthma. This study will seek to better understand if curcumin can be used as an adjunctive therapy for improving asthma control of patients with moderate to severe asthma; a finding we hope will allow for a more affordable treatment.

**Methods:**

This study will utilize a randomized, placebo controlled, double blinded pilot superiority phase 2 trial at an outpatient pulmonary clinic in Southern California, USA. Subjects will be receiving Curcumin 1500 mg or matching placebo by mouth twice daily for the study period of 12 weeks. Subjects will be randomized to either a placebo or intervention Curcumin. Subjects will have 6 clinic visits: screening visit, a baseline visit, monthly clinic visits (weeks 4, 8, and 12), at weeks 4, 8, and a follow-up clinic visit or phone-call (week 16). Changes in asthma control test scores, number of days missed from school/work, FEV1 (% predicted), FEV1/FVC ratio, FVC (% predicted), blood eosinophil count, blood total IgE, and FeNO levels will be compared by group over time.

**Discussion:**

The therapeutic effects of curcumin have been studied on a limited basis in asthmatics and has shown mixed results thus far. Our study hopes to further establish the benefits of curcumin, however, there are potential issues that may arise from our study design that we will address within this paper. Moreover, the onset of the COVID-19 pandemic has resulted in safety concerns that have delayed initiation of our study. This study will contribute to existing literature on curcumin’s role in reducing lung inflammation as it presents in asthmatics as well as patients suffering from COVID-19.

***Trial registration*:**

This study protocol has been approved by the Institutional Review Board at Loma Linda University Health, (NCT04353310). IND# 145101 Registered April 20th, 2020. https://clinicaltrials.gov/ct2/show/NCT04353310.

## Background

Curcumin, a derivative of turmeric (*Curcuma longa*), has been commonly used as a dietary spice and coloring agent. Furthermore, it has been used for centuries in Eastern medicine has been used for centuries in Ayurveda and traditional Chinese medicine to treat anorexia, hepatic disorders, and arthritis [1]. The biologic effects of curcumin include anti-inflammatory, anti-oxidant and anti-neoplastic, mediated by molecular targets including transcription factors, inflammatory cytokines, and proteins involved in cell replication and survival [2]. In vitro and in vivo models have shown that curcumin’s anti-inflammatory effect is mediated by nuclear factor kappa B (NF-κB), a transcription factor that regulates the expression of several genes that are involved in both innate and adaptive immunity and inflammation [3]. Additionally, more recent studies in vitro and in vivo mice models have also discovered that curcumin inhibits cyclooxygenase-2 (COX-2), a key enzyme involved in the development of prostaglandins [4]. Furthermore, it has been shown to inhibit the secretion of proinflammatory Tumor Necrosing Factor-alpha (TNF-α) and Interleukin-6 (IL-6) and anti-inflammatory (IL-10) cytokines [5]. In addition, curcumin has been found to decrease the release of eotaxin, monocyte chemotactic protein 1, and monocyte chemotactic protein 3 from IL-1β stimulated human airway smooth muscle cells [6].

Moreover, when curcumin is added to Dermatophagoides farinae (Der f)–stimulated lymphocyte cell cultures from allergic asthmatic patients, curcumin inhibits Der f– induced lymphocyte proliferation and production of interleukins (IL-2, IL-4, & IL-5), and granulocyte macrophage colony- stimulating factor [7]. It has also be reported that curcumin has an effect on the airways by decreasing the constriction and hyperreactivity when it is administered with ovalbumin [8, 9].

A review of data regarding the biological effects of curcumin in asthma found that most data has been acquired in vitro or in vivo animal models, with only a few observational studies available in humans with discordant results [10]. In one study with mice, inhibition of NF-κB activity reduced airway hyper-responsiveness and inflammatory cell airway infiltration. This was most effective via intraperitoneal administration, and oral administration of curcumin only produced minimal improvement in comparison to controls [11]. In another study with mice, it was shown that curcumin activated the nuclear factor erythroid 2-related factor 2/heme oxygenase 1 (Nrf2/HO-1) signaling pathway in a dose and time-dependent manner, with resulting decline in TNF-α, IL-1β, and IL-6 levels in vitro. Additionally, it was found to decrease eosinophil and white blood count (WBC) in bronchoalveolar lavage, and airway hyper-responsiveness [12], Fig. 1.

**Fig. 1 Fig1:**
[figure not shown]
Diagram that illustrates the mechanism of action of curcumin and the biologic effect

Kim et al. studied a daily dose of 2000 mg based on a previous study by Baum et al. (2008) in patients with Alzheimer [9, 13]. Kim et al. (2011) found that curcumin did not significantly affect in various outcomes such as postbronchodilator Forced Exhaled Volume in 1 s (FEV1), Asthma Control Test scoring, use of rescue bronchodilator, dose of inhaled corticosteroid, exhaled nitric oxide, serum total IgE, or blood eosinophils [9].

Abidi et al. conducted a randomized control trial on 77 patients with mild to moderate bronchial asthma with documented positive bronchodilator reversibility [14]. Curcumin capsules improved airway obstruction evidenced by significant improvement in mean FEV1 values and hematological parameters [14].

The *purpose* of this study will be to identify an adjunctive therapy that is both cost-effective and safe for patients suffering from moderate to severe asthma so as to limit the need for adding more costly medicinal therapies, such as biologics. The *objective* will be to evaluate the effects of oral curcumin supplementation in adult patients with moderate to severe asthma. We *hypothesize* that high-dose supplementation with curcumin will lead to fewer exacerbations and improved control among asthmatics.

## Methods and design

This study will be a randomized, placebo controlled, double blinded pilot superiority phase 2 trial. The rationale for choosing a randomized, placebo control trial is to avoid bias in patient allocation-to-treatment and increase the probability that any differences between groups can be attributed only to the treatment. This study is a pilot study given that there is limited to no data that currently demonstrates curcumin as an effective treatment for asthma.

Recruited subjects will undergo a screening process to ensure they meet the following study criteria listed in Table 1.

**Table 1 Tab1:** Inclusion and exclusion criteria for the study

Inclusion criteria	Exclusion criteria
Male or female, aged 18 and older Physician diagnosed moderate to severe asthma: (GINA 2018) Stable asthma that requires ICS/LABA and/or an additional controller agent (i.e. LTRA, LAMA) Ability to take oral medication and be willing to adhere to the regimen Ability to speak and read English If female and sexually active, should use effective forms of birth control	Current use of turmeric (curcumin) or use within the last 7 days Current use of biologic therapy/immunotherapy/ or bronchothermoplasty Pregnancy or lactation Known allergic reactions to components of turmeric (curcumin) Current use of anticoagulants, and history of coagulopathy or liver disease INR greater than 2.0, PTT greater than 45.0 s

*GINA* Global initiative for asthma, *ICS* inhaled corticosteroids, *LABA* long-acting beta agonist, *LTRA* leukotriene receptor antagonist, *LAMA* long acting muscarinic, *INR* international normalized ratio, *PTT* partial thromboplastin time

All subjects will be screened to ensure meeting inclusion criteria. Screening failure is attained when a participant consents to participate but is not subsequently randomly assigned to either the study intervention or control. In addition, any individual who does not meet the criteria for participation due to meeting exclusion criteria (screening failure) maybe rescreened. Rescreened participants will be assigned the same participant number as for the initial screening.

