### Design

After screening and meeting inclusion and exclusion criteria, subjects will be randomized 1:1 to one of two arms: (1) placebo (n_1_ = 15) or (2) intervention (n_2_ = 15), curcumin. Once assigned into their group, subjects will receive double-blinded study medication to take daily for 12 weeks. In total, subjects will have up to 6 clinic visits: screening visit (D-7 to -1), a baseline visit (V1), three monthly clinic visits (V2-4) and a follow-up clinic visit or phone-call (week 16).

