## Detailed Study procedure

### Baseline

After the subject(s) sign the informed consent, they will undergo history, physical exam including height and weight specifically cardiopulmonary examination, vital signs (blood pressure, heart rate, respiratory rate, and oxygen saturation), and an initial questionnaire that will include current asthma control test and demographics [16, 17]. Subjects will undergo randomization and will then be provided the curcumin or placebo. One member of the study staff will be responsible for randomization but will not share information regarding randomization with the subject nor study staff. Subject will undergo spirometry testing in the clinic site conducted by an experienced respiratory therapist or physician. Effort acceptance criteria is appropriate (American Thoracic Society Grade A—prefer 3 separate efforts with two largest FVC (Forced Vital Capacity) measurements with agreement within 150 mL, and FEV1 (Forced Expiratory Volume in the first second) agreement within 150 mL, B is acceptable if that is the best result after 8 efforts). Spirometer is handheld, and a calibration check will be performed daily with a 3L syringe prior to testing. In addition, Fraction of Exhaled Nitric Oxide (FeNO) will be collected and measured using NIOX VERO® Sensor machines.

Laboratory work will be obtained at the initial visit for plasma eosinophil count and serum total IgE, as well as baseline INR and PTT. Plasma eosinophil count will be drawn in approximately 1.5 mL of blood collected in a lavender top tube. IgE level is minimum 500 µL of blood, although 2 mL is preferred, collected in red tubes (serum) or light green tubes (lithium heparin). Plasma INR/PT and PTT will be collected in 3 mL blue-top tubes. Laboratory specimens will be analyzed via the Loma Linda University Medical Center Clinical Laboratory in compliance with the Clinical Laboratory Improvement Amendments (CLIA) of 1988. Urine pregnancy tests will be conducted for all applicable participants (i.e. females in reproductive age who are not currently on birth control) at baseline, and again at 4, 8 and 12 weeks.

### Visits 2 and 3

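### INR and PTT are exclusion criteria, but they are scheduled only at the randomisation visit and nothing ensures the result is known before randomisation

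*Protocol article*

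**What the plan says.** All references are to the protocol article.

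- **Methods and design, Table 1** lists "INR greater than 2.0, PTT greater than 45.0 s" among the exclusion criteria. The sentence introducing the table says "Recruited subjects will undergo a screening process to ensure they meet the following study criteria listed in Table 1".
- **Design** fixes the order: "After screening and meeting inclusion and exclusion criteria, subjects will be randomized 1:1". It treats screening (Day -7 to -1) and baseline (Visit 1) as separate visits.
- **Detailed Study procedure, Baseline** says "Subjects will undergo randomization and will then be provided the curcumin or placebo". It then goes through spirometry and FeNO, and only after that the laboratory work: "Laboratory work will be obtained at the initial visit for plasma eosinophil count and serum total IgE, as well as baseline INR and PTT".
- **Table 2** has a single mark in the INR and PTT row, under Visit 1, Day 1. The rows for randomisation and for study drug are marked in that same column. The screening cell for INR and PTT is empty.

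**The concern.** An exclusion criterion does its job only if its result is known before the subject is randomised. Here the eligibility text puts the check at screening, while the schedule puts the test at the visit where the subject is randomised and supplied with study drug. If the schedule is followed as printed, a subject who meets one of the trial's own exclusion criteria may already hold a randomisation number and study drug when the result arrives.

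Two things are at stake. One is safety: the coagulation tests are marked only once, so this single draw is the only laboratory check of its kind. The other is the integrity of the randomised set: a subject found ineligible afterwards can be withdrawn and replaced, which swaps a randomised subject for a later one in a trial of 15 per arm.

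**Working it through.** No calculation decides this point. The check sets the relevant statements side by side.

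| Question | Where | Answer in the article |
|---|---|---|
| Are INR and PTT eligibility tests? | Table 1 | Yes, as exclusion criteria |
| When are the criteria checked? | Methods and design | In the screening process |
| Must they be met before randomisation? | Design | Yes |
| When are INR and PTT measured? | Table 2, Baseline | Visit 1, Day 1 only |
| When are randomisation and study drug? | Table 2, Baseline | Visit 1, Day 1 |
| Is a result required before randomisation? | Not stated | No such condition in the article |

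**Step 1: screening.** Of the six visit columns in Table 2, INR and PTT are marked in one, and it is not the screening column. No section allows an earlier value from the medical record to be used instead. So the statement that screening establishes the Table 1 criteria cannot be met for this criterion as scheduled.

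**Step 2: within Visit 1.** Table 2 assigns procedures to visits and gives no order inside a visit. The Baseline section gives one order in its narrative, with randomisation and dispensing first and blood tests last. The samples go to the medical center's clinical laboratory. No turnaround time is given and no bedside test is described.

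**Step 3: a hold on randomisation.** The Randomization and blinding section has the pharmacist assign the next number on a computer-generated list. It does not make that step conditional on a laboratory result.

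**Step 4: what follows an excluding result.** The article defines the term as follows: "Screening failure is attained when a participant consents to participate but is not subsequently randomly assigned to either the study intervention or control". A subject whose result arrives after randomisation is therefore not a screening failure. The Discontinuation of study intervention section lets the investigator withdraw someone found to meet an exclusion criterion that had been missed earlier. The Replacements section then replaces randomised subjects who leave, whether or not they had received study drug.

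**Step 5: size.** The article gives no expected frequency of excluding results, so no count can be derived. One such subject would be 1/15 = 6.7% of an arm, but that is true of any single withdrawal for any reason. It is a unit of scale, not an estimate of the effect of this defect.

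**The case against.** The strongest reply is that Visit 1 can accommodate the right order. The column is labelled as enrolment as well as baseline, and the Design section says explicitly that eligibility precedes randomisation. Drawing blood, reviewing the result and then randomising on Day 1 would satisfy both. The pregnancy test, which also bears on an exclusion, is first marked at Visit 1 too, which suggests that Day 1 may be meant to complete eligibility. **This stands in part.** A reader might infer that eligibility cannot be known at randomisation; the article does not support that. It holds only for the screening visit. What remains is that the favourable order is neither required nor described.

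The Baseline section is also a weak guide to sequence. It includes consent, history and demographics, which Table 2 places at screening, and it puts randomisation ahead of baseline spirometry. **This stands.** The narrative order should not be read as a strict chronology. The finding does not depend on it: the empty screening cell and the absence of any hold are enough.

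Table 1 also excludes anticoagulant users and people with known coagulopathy or liver disease, and both medical history and concomitant medication are reviewed at screening. **This stands as to size.** Most known causes of an abnormal result are removed before Visit 1. It does not remove the point, because the laboratory criterion adds something only for subjects whom the history misses, and those are the ones the schedule may let through.

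A reader might further infer that such withdrawals would bias the treatment comparison. The article does not show that. Removing subjects on a pre-treatment measurement, judged blind and by a uniform rule, would not in itself favour an arm. The article leaves withdrawal to the investigator's discretion and does not expressly place the draw before the first dose, so these conditions are not assured, but no direction of bias can be claimed.

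Finally, this is a condensed article, and release conditions for randomisation numbers may sit in the full protocol or a pharmacy manual. That would excuse silence. It does not excuse a printed schedule that conflicts with the article's own account of screening.

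**Conclusion.** The concern holds as an inconsistency between the eligibility text and the schedule. INR and PTT are exclusion criteria that screening is said to settle, yet they are scheduled only at the visit of randomisation and dispensing, and nothing in the article ensures that the result comes first. Followed as written, the plan permits a subject with an excluding result to be randomised and given study drug, then withdrawn and replaced.

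The number affected is unknown and probably small. That judgement rests on the history-based exclusions working at screening, not on any figure in the article. The conclusion also assumes that no unseen document imposes a hold on randomisation. Nothing here bears on the randomisation method, the endpoints, the sample size or the analysis model, and no view is taken on the threshold values.

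**What to change.** Reconcile the Methods and design section (with Table 1), the Design section, the Baseline section and Table 2, so that the INR and PTT result is on file before the pharmacist releases a randomisation number. Either of two routes would do:

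- mark INR and PTT in the existing screening column of Table 2 and adjust the Baseline text to match; or
- keep the draw at Visit 1, state that randomisation waits until the result has been reviewed, and amend the screening statement to say that this criterion is confirmed at Visit 1.

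The cost is an edit to the schedule and a sentence or two of text, plus one blood draw at screening under the first route or a short wait at Visit 1 under the second. The change belongs before the first subject is enrolled. The Discussion says the study could not take place when originally scheduled, so there may still be time to make it.

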### Study location

One site, outpatient pulmonary academic center in Southern California, United States of America.

### Recruitment strategy

Multiple methods will used to recruit participants in the study. First, flyers will be posted in the medical offices for patients to see. Clinic staff, nursing, and physicians will recruit and identify potential participants. In addition, to ensure meeting NIH policy on inclusion of women and minorities, we anticipate recruiting men, women, and minority groups in equal fashion as indicated in the inclusion criteria (all adults with moderate to severe asthma).

### Design

After screening and meeting inclusion and exclusion criteria, subjects will be randomized 1:1 to one of two arms: (1) placebo (n_1_ = 15) or (2) intervention (n_2_ = 15), curcumin. Once assigned into their group, subjects will receive double-blinded study medication to take daily for 12 weeks. In total, subjects will have up to 6 clinic visits: screening visit (D-7 to -1), a baseline visit (V1), three monthly clinic visits (V2-4) and a follow-up clinic visit or phone-call (week 16).

### Randomization and blinding

Group assignment will be conducted by an independent person (unblinded IDS pharmacist and technician). The unblinded IDS pharmacist will assign the next sequential randomization number assignment from a computer-generated list and dispense assigned study drug in a blinded fashion. This randomization list will be maintained by IDS and not be shared with anyone on the blinded investigator team or blinded subjects. In case of emergency, the study principal investigator, based on clinical judgment, may request the IDS pharmacist to unblind an individual subject’s treatment assignment. Plans to unblind the investigators will occur at the end of the study when data analysis is completed.

### Dosing and administration

Subjects will be receiving curcumin 1500 mg or matching placebo by mouth twice daily for the study period, 12 weeks. Any missed or vomited doses will be skipped and resumed at the next scheduled time. Subjects will use a dosing calendar to record administration or missed doses. The reason for selecting this dose is that curcumin (at 20 mg kg^−1^ bodyweight) was reported to attenuate allergen-induced airway hyper-responsiveness in sensitized guinea pigs [8]. It has been reported that humans can tolerate a dose of curcumin as high as 12 g/day, without any toxic side effects [15]. Therefore, we hypothesize that a dose of 3000 mg curcumin daily may significantly improve asthma control and affect other biomarkers of inflammation.

Sabinsa corporation will be providing the study drugs, both curcumin and matching placebo. Curcumin formulation will include 95% curcuminoids with black pepper extract plus inert excipients. The placebo formulation will contain the same inactive excipients found in curcumin. Both formulations will be identical in appearance. All study drugs will be clearly labeled for use for only this protocol and will not be shared or used for any patients not enrolled in this protocol. All study drug labels will include, *“Caution: New Drug Limited by Federal Law to Investigational Use."* Upon dispensing study drug will be labeled for subject specific use to be administered at home as prescribed by the investigator. All outpatient labels will follow California state Pharmacy laws for prescription drugs and be identified in a blinded fashion.

Study drugs will be stored at room temperature in their original containers for the length of time as instructed by the manufacturer Sabinsa as per their stability testing. Study drugs will be stored per Federal regulations, securely in limited-access pharmacy area and separately from commercial products. Storage temperature will be monitored daily by IDS to ensure proper storage is maintained.

### Concomitant therapy

Current background standard of care treatment for asthma will continue during the study period. Medications to be reported in the Case Report Form are concomitant prescriptions medications, over-the-counter medications, and supplements. Any newly prescribed medications, over the counter or supplements are allowed except for curcumin. Concomitant therapy may affect the outcome as it can alter lab values and perceived side effects.

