### Discontinuation of study intervention

If the subject discontinued using curcumin, this will translate to discontinuation from the study, and remaining study procedures will follow as indicated by the protocol. If a clinically significant finding is identified by the study investigators (including, but not limited to changes from baseline) after enrollment, the investigator or qualified designee will determine if any change in participant management is needed. Any new clinically relevant finding will be reported as an adverse event (AE).

The data to be collected at the time of study intervention discontinuation will include the following: (1) reason for discontinuation of medication, (2) any side effects or symptoms experienced, and (3) cumulative dosage of curcumin ingested at that time.

In addition, participants are free to withdraw from the study at any time upon request, the study investigator may also discontinue or withdraw the participant from the study if any of the following occurred: (1) significant study intervention non-compliance, (2) if any clinical adverse event (AE), laboratory abnormality, or other medical condition or situation occurs such that continued participation in the study would not be in the best interest of the participant, (3) disease progression which requires discontinuation of the study intervention, (4) if the participant meets an exclusion criterion (either newly developed or not previously recognized) that precludes further study participation, and (5) participant is unable to receive curcumin tablets for 12 weeks. Study investigators will document these reasons as Case Report Form.

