During subsequent visits (Weeks 4, 8), subjects will fill out a questionnaire that includes the Asthma Control Test which evaluates the number of severe asthma exacerbations patient has had including: worsening of symptoms for more than or equal to 48 h of consecutive bronchodilator use, any hospitalizations or emergency room visits [16, 17]. The questionnaire will also evaluate the number of missed days from school or work patient has had from asthma. Subjects will undergo spirometry testing in clinic which will be conducted by an experienced respiratory therapist or physician. Exhaled nitric oxide will be measured at that time as well.

### Visit 4

Subjects will fill out a questionnaire that includes the Asthma Control Test, evaluates the number of severe asthma exacerbations patient has had including worsening of symptoms for more than or equal to 48 h of consecutive bronchodilator use, any hospitalizations or emergency room visits. The questionnaire will also evaluate the number of missed days from school or work patient has had from asthma. Participant will undergo spirometry in clinic which will be conducted by an experienced respiratory therapist or physician. Exhaled nitric oxide will be measured at that time. Laboratory work will be obtained at this initial visit to measure plasma eosinophil count and serum total IgE.

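### The concomitant-medication rule expressly allows an anticoagulant to be started on study drug, although current anticoagulant use is an entry exclusion

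*Protocol article*

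**What the plan says.** Three parts of the protocol article bear on this point.

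- **Entry (Methods and design, Table 1).** The exclusions include "Current use of anticoagulants, and history of coagulopathy or liver disease INR greater than 2.0, PTT greater than 45.0 s". Two other treatments are excluded by current use: turmeric or curcumin (also if taken in the preceding 7 days), and "Current use of biologic therapy/immunotherapy/ or bronchothermoplasty".
- **On study (Concomitant therapy).** Background asthma treatment continues and concomitant medication is recorded on the case report form. The rule for new treatment is "Any newly prescribed medications, over the counter or supplements are allowed except for curcumin". The section adds: "Concomitant therapy may affect the outcome as it can alter lab values and perceived side effects".
- **Stopping (Discontinuation of study intervention).** The investigator may withdraw a participant on any of five grounds. Ground (2) covers an adverse event, a laboratory abnormality or another medical condition that makes staying in the trial contrary to the participant's interest. Ground (4) applies "if the participant meets an exclusion criterion (either newly developed or not previously recognized) that precludes further study participation".

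The schedule of activities (Table 2) has a concomitant medication review at screening and at Visits 1 to 4.

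**The concern.** The on-study rule is a general permission with one named exception. An anticoagulant is not that exception, so starting one is allowed on the face of the text. The same drug in use at screening would have excluded the subject. The protocol does not explain why a combination that it bars before Day 1 becomes acceptable afterwards.

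What is at stake is the handling of an individual subject. An investigator who looks up the concomitant-medication rule finds permission and no instruction to stop study drug, check coagulation or consult the stopping rules. An investigator who looks up the stopping rules finds a newly met exclusion listed as a reason to withdraw. Two investigators could treat the same subject differently, and each would be following the protocol.

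**Working it through.** The plan gives no figure to reproduce on this point. The check sets the sections side by side.

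**1. Which entry exclusions carry over into the treatment period?**

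| Current-use treatment exclusion in Table 1 | Excepted from the on-study permission? |
|---|---|
| Turmeric (curcumin) | Yes |
| Biologic therapy, immunotherapy, bronchothermoplasty | No |
| Anticoagulants | No |

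One of three carries over. The anticoagulant row is the point raised here; the second row shows that the same wording reaches further.

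**2. How long does the permission run?** 12 weeks x 7 = 84 days of dosing, at 1500 mg x 2 = 3000 mg of curcumin a day in the active arm.

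**3. Does the Discontinuation section override it?** Not by its terms.

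- The grounds are introduced with *may*, so withdrawal is a choice.
- Ground (4) reaches only an exclusion criterion that rules out continued participation. It does not say whether a new anticoagulant is one, and the Concomitant therapy section points the other way.
- Ground (2) depends on the investigator's judgement of the participant's interest.
- A further sentence obliges the investigator to consider a change in management after a clinically significant finding ("including, but not limited to changes from baseline"). A new prescription is not named as such a finding, and the duty is to decide, not to stop study drug.

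**4. Would the event be noticed?** Yes. The medication review at Visits 2, 3 and 4 would record the drug. No action follows from the record.

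**5. How many subjects?** The article gives no rate. One subject is 1/30 = 3.3% of the planned 30. If, as an assumption, the number ranged from one to three, that would be 3.3% to 10% (3/30). The plan's 30% attrition allowance is 0.30 x 30 = 9 subjects.

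**The case against.** The strongest reply is that the two sections do different jobs. One says what a subject may be prescribed, and needed anticoagulation should never be forbidden. The other says who may stay on study drug, and grounds (2) and (4) both give room to withdraw someone who has developed a reason for anticoagulation. With the medication review at each visit, a careful investigator would reach the right decision. This has force: it makes the practical risk small and shows that the protocol is not without a safeguard. It does not remove the conflict, because the permission is explicit, withdrawal is optional, and neither section refers to the other.

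It can also be said that a journal article leaves prohibited-medication lists to the full protocol. That would answer an omission. Here the article states the rule and states it too broadly.

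A reader might go further and infer that the trial needs routine coagulation monitoring. The tests are described as "as well as baseline INR and PTT", Table 2 marks them at Visit 1 only, and for Visit 4 the text reads "Laboratory work will be obtained at this initial visit to measure plasma eosinophil count and serum total IgE". The documents do not support that step. INR and PTT serve as eligibility limits, for which one measurement at entry is consistent. Nothing in the article says that curcumin alters coagulation, and no coagulation endpoint is planned. A week 12 test would also come at the end of dosing, too late to guide it.

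**Conclusion.** The point holds as a conflict between two stated rules: anticoagulant use is barred at entry and expressly permitted on treatment, and the stopping rules allow withdrawal without requiring it. It is a low-priority safety correction. It rests on the text alone, and on the assumption that the entry exclusion was meant to keep anticoagulants and study drug apart, since the article gives no reason for it.

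Two stronger readings should be avoided. The article does not state or quantify a bleeding risk with curcumin; it reports human tolerability up to 12 g/day. Nor does it require a subject on a new anticoagulant to stay on study drug. The number of subjects affected cannot be derived from the document and may be zero. Neither the planned efficacy analysis nor the sample size calculation depends on this point.

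**What to change.** Replace the permission in Concomitant therapy with wording such as:

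> *New prescription drugs, over-the-counter products and supplements may be used, except curcumin, anticoagulants and the other therapies excluded in Table 1. If an anticoagulant is clinically needed, it is given, study drug is stopped or held, and INR and PTT are checked. The subject is then handled under Discontinuation of study intervention.*

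Needed anticoagulation is not withheld; the instruction concerns study drug. Naming the other Table 1 therapies closes the same gap for biologics and immunotherapy in the same sentence.

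The cost is a short text change, plus one unscheduled INR/PTT check for each subject who starts an anticoagulant. There may be one or a few more discontinuations, which the existing Replacements section already covers. No scheduled visit or routine test is added.
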